### Randomization to treatment groups

The randomization sequence will be computer-generated, stratified by nurse and blocked in groups of two. Study nurses will call the research units to give patient identification numbers and will be told the randomly assigned patient allocations. After this, participants in the intervention group will be scheduled for their first intervention visits.

The outcome assessors, data analyst, and physician will be blinded to patient allocation. To evaluate the effectiveness of blinding, these individuals will be asked to choose the arm to which they believed each patient was assigned (possible answers: intervention, usual care, or unknown). If they answered "intervention" or "usual care", they were asked to indicate what led to that belief.

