### Multifactorial Intervention

The intervention consists of five components that will be delivered during three interventional visits of about 30 min each. Use of a detailed intervention protocol and comprehensive motivational interview training is intended to increase the effectiveness of interventions. The study nurses will carefully document each component of the multifactorial intervention that they perform by use of specially designed intervention visitation documents and will register the time and the duration of each component of the intervention.

The five components of the intervention are:

1. ***Motivational interview: ***This will be based on the Health Belief Model [24] and the Prochaska and DiClemente stage of change [25], and will try to resolve ambivalences that patients have regarding medication and explore perceptions that patients have about their ability to control events (locus of control).

2. ***Pillbox Reminder: ***A pillbox organizer with seven compartments will be given to the patients. They will self-fill it with one pill for each day of the week. Use of the pillbox will be explained to patients in the intervention group.

3. ***Family Support: ***Patients will designate one person in their household who will be responsible for reminding and monitoring medication intake. The designated person must accept responsibility of reminding the patient to take medication and of supervising pill intake. If a patient lives alone or does not wish to involve a family member or carer, they do not need to designate anybody. Thus, this part of the intervention is not mandatory.

4. ***BP measurements and AHT reminder forms: ***Twelve forms (one per month) and a table will be completed by the patient and nurse and used to record the date and hour of all BP readings (including gaps). AHT dosage and a telephone contact number will also be recorded on each form. This information will be frequently updated. The forms will be provided to patients and nurses at visit 0, and patients will be asked to bring them to all subsequent visits.

5. ***Simplification of dosing regimens: ***AHT dosage will be recorded at visit 0, and pharmacists will simplify the dosing regimen when possible at subsequent visits.

Visit 1 (first month, 40 min total): motivational interviewing (25 min), pill reminder (5 min), self-recording of BP (5 min), family support, when possible (5 min).

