### Statistical Analysis

The primary statistical analysis will determine if our multifactorial intervention to improve AHT adherence is effective in lowering systolic BP and if the intervention is cost-effective. We will use intention-to-treat analysis for all data analyses; that is, all randomized patients will be included in the analysis, regardless of participation in any treatment sessions. This approach reduces the bias that may occur when participants who do not receive assigned treatments are excluded from analysis. All tests will be two-sided and α-values of 0.05 will be considered statistically significant.

We will test for significant differences between baseline characteristics of control and intervention groups. We will perform descriptive analysis, with continuous variables summarized by their means and standard deviations for normal distributions, and by median and 25^th ^and 75th percentiles for non-normal distributions.

In bivariate analysis, we will compare systolic and diastolic BP between the intervention and control groups at visit 4 (12th month) using the Student's *t*-test if both sample groups had normal distributions or the Mann-Whitney U test against the usual null hypothesis of no difference between means if the sample groups had non-normal distributions. We will also calculate 95% confidence intervals to assess the clinical significance of our treatment.

In multivariate analysis, we will adjust for clinical inertia (physicians blinding and number of medication changes) in a multiple linear regression model.

We will test for a significant difference in the percentage of patients with controlled BP (according to ESH/ESC guidelines) in the intervention and control groups using the χ^2 ^test. We will estimate relative and absolute risk reduction and the number needed to treat, defined as the estimated number of patients who need to be treated with the intervention (rather than the usual care) for one additional patient to be controlled. The 95% confidence intervals for these calculations will be provided. The number needed to treat is calculated as the reciprocal of the difference between the proportion of patients controlled in the intervention group and the control group.

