### Limitations

Control patients are allowed to visit study nurses during the study period so "contamination" of the control group is possible. This would reduce the point estimate of the intervention's effectiveness and may lead to a type II error. In other words, an effective intervention could be classified as ineffective because the observed effect size was neither statistically nor clinically significant. We will try to overcome this problem by using a large sample size (n = 320) based on the assumption that there will be a 15% contamination rate.

Clinical inertia is an important factor associated with poor BP control [7]. As relevant to our study, physicians of the intervention patients may be more prone to change medications if they know that their patients are involved in a clinical trial of BP control. The possibility of this effect will be significantly reduced by blinding physicians to patient allocation. However because patients are not blinding to treatment, physicians could easily find out patient allocation. We will retrospectively review the medication records to determine if there were differences in the number of medication changes in the two treatment arms and we will evaluate the effectiveness of the blinding by direct interview. We will control in a multivariate analysis by number of medication changes and physicians blinding (yes/no).

There will be a tendency of BP values, when selecting patient non optimally controlled, to resemble their mean. Randomized trials with a control group avoid regression toward the mean because BP values fell in both treated and placebo groups, but it fell by more in the treated group.

In most non-pharmacological randomized controlled trials where follow-up visits are part of the intervention, follow-up visits in the control group are common. Thus, an undesirable "Hawthorne effect" could mask the effects of our intervention. To avoid this problem, the effects of the intervention will be compared with a control group without protocol-stipulated follow-up visits.

The ideal outcome measures for our trial are reduction of cardiovascular events and/or total mortality. However, such a study would be very expensive because it would require a very large sample size and very long study period. The use of clinically relevant reduction of BP (a surrogate marker) allows us to perform this study with a more manageable number of patients (n = 320) in a relatively short period of time (12 months).

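### The multivariable BP model adjusts for two post-randomisation variables that allocation may affect, and the plan does not say whether it or the unadjusted comparison decides effectiveness

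*Protocol article*

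**What the plan says.** The Statistical Analysis section plans two analyses of 12-month blood pressure. The first is unadjusted: a t-test or Mann-Whitney test between arms, with 95% confidence intervals. The second is multivariable: "we will adjust for clinical inertia (physicians blinding and number of medication changes) in a multiple linear regression model". Limitations repeats the commitment: "We will control in a multivariate analysis by number of medication changes and physicians blinding (yes/no)". These are the only covariates that the article names for the BP regression.

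The article also says how the two covariates arise:

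- **Medication changes.** "We will retrospectively review the medication records to determine if there were differences in the number of medication changes in the two treatment arms" (Limitations).
- **Physician blinding.** Outcome assessors, the analyst and the physician are covered by this statement: "these individuals will be asked to choose the arm to which they believed each patient was assigned" (Randomization to treatment groups). The permitted answers are intervention, usual care or unknown. Limitations adds a direct interview.

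The article does not say which of the two analyses is the main result.

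**The concern.** A regression that compares randomised arms keeps the protection of randomisation only if its covariates could not have been altered by the arm. Here both are recorded during or after follow-up, and the protocol gives reasons why each might differ by arm.

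If the intervention changes how often drugs are altered, and alterations change blood pressure, holding the number of alterations fixed removes part of the intervention's effect. If poorly controlled patients also receive more alterations, conditioning on the count mixes in differences in severity between arms. The coefficient can then move either way.

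What is at stake is the reading of the primary outcome. Limitations presents the adjusted model as the way to deal with clinical inertia, so a reader could take it as the corrected and more credible answer. If the two analyses disagree, no stated rule settles which one counts.

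**Working it through.** The plan has no figure of its own to reproduce on this point. The check has two parts.

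**1. Does the protocol give the causal paths?**

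| Path | Source |
|---|---|
| Allocation to physician knowledge | "because patients are not blinding to treatment, physicians could easily find out patient allocation" (Limitations) |
| Participation or arm to medication changes | "physicians of the intervention patients may be more prone to change medications if they know that their patients are involved in a clinical trial" (Limitations) |
| Intervention component to regimen changes | "pharmacists will simplify the dosing regimen when possible at subsequent visits" (Multifactorial Intervention; Table 1 lists it for the intervention group) |
| Medication changes to blood pressure | "Clinical inertia is an important factor associated with poor BP control" (Limitations) |

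The first, second and fourth rows make medication changes a possible mediator on the protocol's own reasoning. The third applies only if pharmacist simplifications are counted as changes, which the article does not say.

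**2. How large could the distortion be?**

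Write SBP = constant + d·A − b·M + c·U + error. A is arm, M the number of changes, b the mmHg fall per change, and U an unmeasured severity that raises both M and SBP. With Δ the arm difference in mean M, the total effect is d − b·Δ. From the protocol: target 6 mmHg, SD 15 mmHg, and 320 patients with 20% loss, so 160 × 0.8 = 128 analysed per arm. Everything else below is assumed.

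*Illustration A.* One change per control patient at U = 0, b = 3 mmHg, physician unblinded for 10% of control and 40% of intervention patients, and d set so that the total effect is −6. Without U the adjusted model should return d = −6 + 3Δ. With U, severity is worth 8 mmHg per SD and 0.4 on the log rate of changes. Each row is the mean of 3,000 simulated trials; multipliers apply to the change rate.

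| Intervention arm changes | d, no U | Adjusted, no U | d, with U | Adjusted, with U |
|---|---|---|---|---|
| +0.5 (×1.5) | −6 + 1.5 = −4.5 | −4.46 | −4.38 | −5.85 |
| +0.3 (×1.3) | −6 + 0.9 = −5.1 | −5.07 | −5.03 | −5.85 |
| 0 | −6.0 | −5.98 | −6.00 | −5.95 |
| −0.3 (×0.7) | −6 − 0.9 = −6.9 | −6.85 | −6.97 | −6.11 |
| −0.5 (×0.5) | −6 − 1.5 = −7.5 | −7.50 | −7.62 | −6.17 |

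Regression on arm alone gave −5.94 to −6.08 throughout. Without U the adjusted estimate misses the total effect by up to 3 × 0.5 = 1.5 mmHg. With U the two distortions nearly cancel. The estimate then lies close to −6 by coincidence of the inputs, and it no longer recovers d when the arms differ in changes.

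*Illustration B.* d = −6, severity worth 7 mmHg per SD and a 1.42-fold change rate per SD, and about one change per patient. Only medication changes are adjusted for. Two scenarios: 40% of intervention patients have one simplification counted as a change (with no BP effect of its own), or the intervention arm has 30% fewer changes.

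| b (mmHg per physician change) | 40% simplified: unadjusted / adjusted | 30% fewer: unadjusted / adjusted |
|---|---|---|
| 0 | −5.97 / −6.76 | −6.0 / −5.34 |
| 2 | −6.00 / −6.06 | −5.39 / −5.33 |
| 3 | −6.03 / −5.72 | −5.11 / −5.34 |
| 4 | gap 0.5–0.7, sign reversed from b = 0 | gap 0.5–0.7, sign reversed from b = 0 |

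The gap is 0.6 to 0.8 mmHg when changes have no effect on SBP, under 0.1 at 2 mmHg per change, and opposite in sign by 3 mmHg. If simplifications are not counted, the first scenario shows no bias (−5.96 unadjusted, −5.97 adjusted at b = 0).

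**The case against.** The strongest reply is that the effect by randomised arm is already planned and untouched. The sample size rests on the between-arm difference, and the unadjusted test comes first. The control-rate comparison, risk reductions and number needed to treat do not use this regression. No sentence says that the regression overrides the unadjusted result. Its purpose, checking for differential co-intervention when patients are unblinded, is also reasonable. All of this stands, and it confines the point to one model of undeclared status.

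Several stronger readings are tempting, and the document does not support them:

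- **That the adjusted effect is certainly biased.** Bias in the total effect vanishes if allocation affects neither covariate. The protocol describes a possible mechanism, not an established fact.
- **That the count is partly the intervention itself.** This needs pharmacist simplifications to be included; Limitations speaks of physicians changing medication.
- **That physician blinding is nearly a proxy for arm.** A physician may guess correctly in either arm or answer unknown, and no unblinding rates are given.
- **That the model must lose precision.** Standard errors inflated by a factor of 1.10 or 1.24 follow from assuming 40% or 60% unblinding in the intervention arm against 5% in control. Those splits are assumptions.
- **That the model breaches the intention-to-treat commitment.** The protocol defines that as keeping all randomised patients in their assigned arms, which the regression can do. The objection is to what its coefficient estimates.
- **That baseline covariates are excluded.** The article names none for this model, but it is a condensed account, and nurse effects are already planned through multilevel analysis.

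**Conclusion.** The point holds for the multivariable BP regression and for the missing ranking of analyses. Both named covariates arise after randomisation, and the protocol accepts that allocation may affect them. If it affects either, the adjusted arm coefficient does not in general estimate the effect by randomised assignment, and confounding by indication prevents a clean direct-effect reading.

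No single magnitude can be defended. Differences ran from near zero to about 0.8 mmHg in either direction with a common cause of changes and BP, and up to 1.5 mmHg without one, against a 6 mmHg target. These depend on assumed change rates, BP effect per change and severity, none of which the document gives. The unadjusted 12-month comparison is sound on this point. The practical risk is that the adjusted result is read as the better answer.

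**What to change.** Make four wording changes in Statistical Analysis and Limitations:

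1. State that effectiveness on systolic BP is judged by the 12-month comparison by randomised arm, with any adjustment limited to pre-randomisation variables: baseline systolic BP and nurse, the stratification factor.
2. Remove number of medication changes and physician blinding from that model.
3. Report medication changes by arm, with pharmacist simplifications counted separately from physician changes, and report physicians' blinding guesses by arm.
4. If the inertia-adjusted regression is kept, label it exploratory and state that it cannot alter the main conclusion.

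The cost is a few sentences. Baseline BP is measured at visits −1 and 0, nurse is known from the stratification, and the medication review and blinding questions are already planned. The only extra work is to record the source of each medication change during the review.

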### Limitations

Control patients are allowed to visit study nurses during the study period so "contamination" of the control group is possible. This would reduce the point estimate of the intervention's effectiveness and may lead to a type II error. In other words, an effective intervention could be classified as ineffective because the observed effect size was neither statistically nor clinically significant. We will try to overcome this problem by using a large sample size (n = 320) based on the assumption that there will be a 15% contamination rate.

Clinical inertia is an important factor associated with poor BP control [7]. As relevant to our study, physicians of the intervention patients may be more prone to change medications if they know that their patients are involved in a clinical trial of BP control. The possibility of this effect will be significantly reduced by blinding physicians to patient allocation. However because patients are not blinding to treatment, physicians could easily find out patient allocation. We will retrospectively review the medication records to determine if there were differences in the number of medication changes in the two treatment arms and we will evaluate the effectiveness of the blinding by direct interview. We will control in a multivariate analysis by number of medication changes and physicians blinding (yes/no).

There will be a tendency of BP values, when selecting patient non optimally controlled, to resemble their mean. Randomized trials with a control group avoid regression toward the mean because BP values fell in both treated and placebo groups, but it fell by more in the treated group.

In most non-pharmacological randomized controlled trials where follow-up visits are part of the intervention, follow-up visits in the control group are common. Thus, an undesirable "Hawthorne effect" could mask the effects of our intervention. To avoid this problem, the effects of the intervention will be compared with a control group without protocol-stipulated follow-up visits.

The ideal outcome measures for our trial are reduction of cardiovascular events and/or total mortality. However, such a study would be very expensive because it would require a very large sample size and very long study period. The use of clinically relevant reduction of BP (a surrogate marker) allows us to perform this study with a more manageable number of patients (n = 320) in a relatively short period of time (12 months).

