**Figure 1 F1:**
[figure not shown]
**Study design Flow-chart**.

Table 1 summarizes the measures and variables according to the timeline. Participants will be studied for 1 year following randomization. Primary and secondary outcomes will be assessed by an external nurse who will be blinded to treatment assignment after 12 months. The primary outcome will be systolic BP. Secondary outcomes will include diastolic BP, direct costs, and the number of patients who required treatment to yield one patient with normalized BP.

**Table 1 T1:** Measures, variables and timeline

VISIT	-1	0	1	2	3	4
Time (months)	-1	0	1	3	9	12
Blood pressure measurement inclusion criteria	X	X				
Morisky-Green and Haynes-Sackett tests	X					
Inclusion and exclusion criteria	X					
Comorbidities		X				
Blinded blood pressure measurement						X
Medication use						X
Adverse effects to medication		X				X
Medical consultation, cardiovascular events and hospital admission.						X
Checklist and time duration of intervention components (Intervention group)			X	X	X	
Motivational interview (Intervention group)			X	X	X	
Pill reminder (Intervention group)			X			
Family support (Intervention group)			X	X	X	
Blood pressure self-recording (Intervention group)			X	X	X	
Simplification of dosing regimens (Intervention group)			X			

Information bias will be minimized by use of a design that provides the maximum possible level of masking for studies of non-pharmacological intervention. In particular, the outcome assessor, data analyst, and physician will all be blinded to patient allocation. Misclassification, if any, is expected to be non-differential. Quality control will include recording of patient adherence to interventions, inclusion and follow-up monitoring, and quality supervision of data entry. We will perform an intention-to-treat analysis of the data; that is, the analysis will be by randomized assignment regardless of participation in intervention sessions.

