Visit 2 (third month, 35 min total): motivational interview (25 min), simplification of dosing regimen, if possible, check of self-recording BP (5 min), family support, when possible (5 min).

Visit 3 (ninth month, 35 min total): motivational interview (25 min), check self-recording BP (5 min), and family support, when possible (5 min).

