### Control group

Patients randomized to the control group will not receive any changes in their care. However, they will be contacted at baseline and at the 12th month and asked to complete the same outcome measures as the intervention group.

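### The count of medication changes used as the marker of physician co-intervention may include the pharmacist simplification that is itself part of the intervention

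*Protocol article*

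**What the plan says.** Component 5 in the Multifactorial Intervention section reads: "AHT dosage will be recorded at visit 0, and pharmacists will simplify the dosing regimen when possible at subsequent visits". Table 1 assigns this row to one arm ("Simplification of dosing regimens (Intervention group") and marks it at visit 1. The visit schedule in the text lists it at visit 2 instead: "motivational interview (25 min), simplification of dosing regimen, if possible". For the other arm, the Control group section states: "Patients randomized to the control group will not receive any changes in their care".

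The Limitations section identifies a possible co-intervention: "physicians of the intervention patients may be more prone to change medications". Its check is the arm comparison of record-based counts: "We will retrospectively review the medication records to determine if there were differences in the number of medication changes in the two treatment arms". Limitations then says that the number of changes and physician blinding will be controlled for in a multivariate analysis. Statistical Analysis repeats this as a multiple linear regression adjusted for clinical inertia, defined by those two variables.

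**The concern.** The check is meant to detect what physicians do. The quantity chosen is the number of medication changes, whoever made them and for whatever reason. One arm has a protocol-directed source of regimen changes that the other lacks. If those changes are recorded as medication changes, an excess in the intervention arm has two possible explanations that the bare count cannot separate: physicians treated those patients more actively (a bias), or pharmacists delivered component 5 (the treatment). The better component 5 is delivered, the more biased the trial would appear.

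Two results are at stake. The arm comparison could lead readers to discount a real effect as co-intervention. The regression would adjust for a variable that is partly a consequence of allocation, so the adjusted effect could differ from the effect of the whole intervention.

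**Working it through.** The protocol states no figure on this point, so there is none to reproduce. The structure comes from the text; every rate below is an assumption.

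**Inputs from the protocol.** 320 patients, equal allocation: 320 / 2 = 160 per arm. Loss to follow-up 20%: 160 × 0.8 = 128 completers per arm.

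**Assumed inputs.** Mean physician-initiated changes per patient, λ, the same in both arms (0.5 to 1.5). Proportion of intervention patients with one recorded simplification, s (10% to 50%).

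**Step 1: expected counts.** Control mean = λ. Intervention mean = λ + s. The difference is s, although physicians behave identically.
- Extra changes in 160 patients: 0.10 × 160 = 16 to 0.50 × 160 = 80.
- Apparent ratio (λ + s) / λ for s = 10% and 50%:
  - λ = 0.5: 1.2 and 2.0
  - λ = 1.0: 1.1 and 1.5
  - λ = 1.5: 1.07 and 1.33

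**Step 2: chance of a false signal.** With Poisson physician changes and at most one simplification per patient, the standard error of the difference is √[(2λ + s(1 − s)) / 128]. For λ = 1.0 and s = 0.20 it is √(2.16 / 128) = 0.130, so the expected z is 0.20 / 0.130 = 1.54. The chance of exceeding 1.96 is then about 34%. Simulation with a Welch t-test (128 per arm, two-sided 5%) gave these rates of p < 0.05 with no true physician difference:

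| s | λ = 0.5 | λ = 1.0 | λ = 1.5 |
|---|---|---|---|
| 0 | 5% | 5% | 5% |
| 10% | 19% | 13% | 10% |
| 20% | 57% | 34% | 24% |
| 30% | 87% | 64% | 47% |
| 50% | 100% | 96% | 88% |

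The row s = 0 is what a count restricted to physician-initiated changes would give.

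**Step 3: the adjusted model.** Assume a true effect of 6 mmHg (the planned difference), λ = 1.0, and g mmHg lower systolic pressure per physician change. Regressing on arm and the unrestricted count gives a count coefficient of about −g / [1 + s(1 − s)/2], because half the patients (the intervention arm) carry the extra variance s(1 − s). The arm effect then shrinks by about g·s / [1 + s(1 − s)/2].
- g = 3, s = 0.20: 0.60 / 1.08 = 0.56, leaving 5.4 mmHg (simulated 5.4).
- g = 5, s = 0.50: 2.50 / 1.125 = 2.22, leaving 3.8 mmHg (simulated 3.8).
- g = 0: no shrinkage (simulated 6.0).

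Adjusting for physician changes alone gave about 6.0 throughout. The direction depends on the sign of g. If patients with higher pressure receive more changes, so that the count is associated with higher final pressure, the same algebra moves the estimate the other way.

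**Step 4: what is untouched.** The 12-month comparison of systolic pressure by t-test or Mann-Whitney test does not use the count.

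**The case against.** The strongest reply is that the key premise is not documented. The protocol does not define a medication change, does not say that a simplification would be logged as one, and makes simplification conditional on its being possible. A reader might infer that the count is certain to include the intervention; the text supports only that it may, unless simplifications are excluded. That limit stands.

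A second reply is that clinical inertia is a prescriber concept, so the count could be read as physician-initiated changes only, with coding left to a fuller document. This has some force. But the article does fix the measure, twice, as an unrestricted number, and that number conflicts with a component described in the same article. If only the total is recorded, the initiator cannot be recovered from it later.

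A third reply is that nurses document each component delivered, on a checklist scheduled at visits 1 to 3. It would therefore be wrong to infer that the trial has no means of separating the sources. But the article does not say the two will be linked. The checklist also exists in one arm only: using it to delete changes would remove them from that arm alone, and could bias the comparison the other way.

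A reader might also infer that component 5 undermines the statement that "the outcome assessor, data analyst, and physician will all be blinded to patient allocation". This does not add a finding. Limitations already concedes that physicians could easily learn the allocation, and the blinding questionnaire asks what led to the belief.

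**Conclusion.** The point holds as a defect in a bias check and in the adjusted analysis. As written, the marker of physician co-intervention may count delivered treatment, and nothing in the protocol excludes it. With equal physician behaviour, the expected excess per patient equals the proportion with a recorded simplification. That proportion is not given, so the size is unknown. The 16-80 extra changes, the false-signal rates and the adjusted effects of 5.4 to 3.8 mmHg illustrate assumed rates and are not predictions. The lower adjusted effects also require that physician changes lower pressure.

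A reader might go further and infer that the primary result is compromised. The documents do not support that, because the main 12-month comparison is unadjusted. What can mislead is its interpretation and the adjusted estimate reported beside it. The change should be made before the record review begins.

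**What to change.** - In the planned record review, code every medication change in both arms by the same rule: by type (drug added, drug stopped, dose changed, regimen simplified) and by who initiated it. Keep the coder unaware of arm where possible.
- Base the Limitations comparison and the clinical inertia variable in Statistical Analysis on physician-initiated changes other than simplification.
- Report simplifications separately. Use the intervention checklist only to describe delivery of component 5, not to remove changes from one arm.
- Reconcile Table 1 (visit 1) with the visit schedule (visit 2) on when simplification takes place, because the timing helps to identify these changes.

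The cost is two coding fields in a review already planned, with no added patients or visits. Some changes will be hard to classify. Coding the initiator may partly reveal allocation, so the coder should not be the blinded outcome assessor or the data analyst.
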